### Interim analyses

No interim analysis has been planned because the interventions delivered have been proved feasible and safe for the intended population.

### Methods for additional analyses (e.g. subgroup analyses)

As an ancillary analysis, differences in effect pending on clusters will be examined.

### Methods in analysis to handle protocol non-adherence and any statistical methods to handle missing data

The analyses of outcomes follow the intention-to-treat principle. Missing outcomes will be imputed with multiple imputation [41]. For non-adherence to protocol, non-response analyses will be performed for excluded patients and non-completers. A per-protocol analysis will be conducted as a sensitivity analysis.

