## Background and rationale

A hip fracture is a serious event for older adults since approximately 50% do not regain their habitual level of physical function thus, acquiring new or additional need for care [1, 2]. Furthermore, when compared to an age-matched group, the 1-year mortality increases threefold and the quality of life is reduced [2, 3]. The 30-day readmission rate after a hip fracture is as high as 16–19% [4, 5].

For older adults, it is well-known that poor mobilisation and reduced activity during and after hospitalisation trigger loss of muscle mass that moreover is associated to increased mortality [3]. To reduce mortality, early detection of illness and sufficient pain management has been identified as important **[**6**,**
7**]**. Insufficient pain management is associated to an increased risk of complications, morbidity, and mortality and also impedes physical activity [8]. Nevertheless, continuous and progressive rehabilitation, as well as the detection of critical illness and complications, is lacking across the sectors in a healthcare system divided into two financial and self-governing sectors.

In Denmark, the average length of stay is 5–7 days for hip fracture patients [7]. Rehabilitation in the primary sector must be initiated within 7 days after discharge. However, usual care does not include systematic assessment including vital signs measurement. Furthermore, various exercise regimes are used depending on the sectors, and the regimes are usually not specified in terms of intensity or progression. Communication and cooperation between sectors are also lacking, although the older adults express a need for increased involvement [9].

To impede functional decline and lower mortality and readmission rates, continuous and progressive rehabilitation and care across sectors are needed. This study introduces an empowerment-orientated praxis focusing on continuous rehabilitation and care, as well as optimised communication and cooperation between sectors.

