An empowerment-orientated practice requires a change in the healthcare professionals’ approach towards seeing the older adults as a partner capable of acting and taking responsibility [16]. To implement the empowerment-orientated praxis, two initiatives are used: first, the patients will be given access to knowledge [16]. The older adults will receive a trolley containing the rehabilitation regime, exercise equipment, and a guide, targeted patient and next-of-kin to a digital healthcare app. The app contains videos and informative interviews with doctors and nurses from the ortho-geriatric ward and health professionals from the municipalities [17, 18]. Second, health professionals will participate in a workshop where they will learn about empowerment and how to use it. During the workshop, the health professionals will also be informed on the importance of strength training and measuring vital signs and pain and introduced to the rehabilitation regime. The intervention is described using the Template for Intervention Description and Replication (TIDieR) [19] (Table 2).

**Table 2 Tab2:** Description of intervention and comparator using TIDieR

	Rehabilitation for life	Usual rehabilitation and care
Why	Continuous and progressive rehabilitation as well as early detection of critical illness and complication during and after hospitalisation will improve the older adults’ physical performance and decrease mortality. Knowledge empowers older adults and facilitates a change in mindset among health professionals.	Activity-based rehabilitation restore and maintain the activities of daily living. Older adults’ need to regain functions creates motivation.
What	25 rehabilitation sessions with a physiotherapist over 12 weeks of these 5 within 2 weeks from discharge are planned. A virtual meeting between physiotherapist in the primary and secondary sectors and older adults is conducted in the 2 rehabilitation sessions after discharge. The suitcase contains knowledge and equipment the older adults need to take responsibility and perform daily exercises. Health professionals participate in a workshop. Early detection of critical illness and complications performed day 3 after discharge.	Older adults’ general amount of rehabilitation is approximately 1–2 rehabilitation sessions a week for 6–8 weeks. Care has to be prescribed.
Who provide	Physiotherapists, nurses, and social- and health assistants.	Physiotherapists, nurses, and social- and health assistants.

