### Outcome

#### Primary outcomes

The primary outcome for the physical function is Timed Up and Go [20] 8 weeks after discharge.

As the study is organised across two sectors, the CAS score measured 30 days after discharge makes a second primary outcome.

TUG is a valid and reliable test that measures the time it takes a person to get up from a chair with an armrest, walk 3 m, return to the chair, and sit [21]. The standard error of measurement (SEM) for patients with hip fractures is 11% [9]. It is hypothesised that patients in the intervention group will achieve a significantly reduced TUG score compared to usual care.

The CAS assesses mobility by (a) getting in and out of bed, (b) sit to stand, and (c) gait with a usual walking aid. It is hypothesised that a significantly larger number of patients in the intervention group will have a CAS = 6 at 30 days post-surgery compared to the control [22].

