### Sample size

The annual enrollment of patients with hip fractures from the six municipalities was a mean of 392. With an assumption that 50% of patients fulfilling the inclusion criteria (196 of 392), 48 patients will be available for inclusion every 3 months equal to eight patients per cluster. However, due to frailty, a 20% dropout is expected. Based on these assumptions, we expect approximately six patients per cluster every 3 months for the trial equal to a total of 330 patients.

The power calculation for the TUG is based on a reduction of 25% [36] and an estimated TUG score at discharge of 21.1 s (9.2) [37, 38]. With six patients per cluster every quarter, estimated power is 89%. Interclass coefficient [39] is 0.01, and *α* is 0.05. Thus, patient recruitment period will be 21 months.

For CAS, the power calculation is based on a 25% increase in the proportion of older adults who, 30 days post-surgery, have a CAS score = 6, power equals 90%.

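### Multiple imputation is set for missing outcomes with no exception for death (both primary outcomes) or inability to do the test (TUG)

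*Protocol article*

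**What the plan says.** The section *Methods in analysis to handle protocol non-adherence and any statistical methods to handle missing data* sets the analysis principle: "The analyses of outcomes follow the intention-to-treat principle". It then gives one rule for gaps: "Missing outcomes will be imputed with multiple imputation". For non-adherence it adds that "non-response analyses will be performed for excluded patients and non-completers", without saying what outcome values such patients carry. The only sensitivity analysis it names is this: "A per-protocol analysis will be conducted as a sensitivity analysis".

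Four other places bear on the rule:

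- *Sample size* states that "due to frailty, a 20% dropout is expected".
- *Background and rationale* opens its case for the programme with the words "To impede functional decline and lower mortality and readmission rates". Table 2, under *Intervention description*, expects the programme to improve "physical performance and decrease mortality".
- *Primary outcomes* defines TUG as a test that "measures the time it takes a person to get up from a chair with an armrest", walk 3 m, return and sit. The second primary outcome is CAS, which scores bed transfer, sit-to-stand and gait; success is CAS = 6.
- *Other outcomes* records mortality as an event in its own right and does not link it to either primary analysis.

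**The concern.** Multiple imputation is meant for values that exist but were not recorded. A TUG time for a patient who has died, or who cannot rise and walk 3 m, does not exist. Nor does a 30-day CAS for a patient who died before day 30. Under intention to treat with an unqualified imputation rule, such patients would be given values predicted from patients who lived and could be tested.

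This matters more here than in many trials. Dropout is put down to frailty, so the protocol's own explanation ties missingness to the function being measured. *Eligibility criteria* set no walking requirement. The intervention is tailored for patients with CAS of 4 or more, which implies that patients below 4 can be enrolled. The programme also aims to reduce deaths. If it does, the arms differ in exactly the patients whose values would be invented, and a real benefit could be hidden. If death or inability is instead more common under the intervention, a harm could be hidden. A per-protocol analysis does not examine either possibility.

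**Working it through.** **1. The plan's own TUG figure.** Inputs from *Sample size*, *Study setting* and *Trial design*: planned effect 0.25 × 21.1 = 5.275 s, SD 9.2 s, intraclass correlation 0.01, alpha 0.05 (taken as two-sided), six clusters, six patients per cluster per quarter, and 21 months / 3 months = 7 periods. One cluster crossing per step is assumed, because Fig. 1 is not shown.

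Hussey–Hughes variance: I·σ²(σ² + Tτ²) / [(IU − W)σ² + (U² + ITU − TW − IV)τ²]

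- τ² = 0.01 × 9.2² = 0.846; σ² = 0.99 × 9.2² / 6 = 13.966
- I = 6, T = 7, U = 21, W = 91, V = 91
- Numerator: 6 × 13.966 × (13.966 + 7 × 0.846) = 1,666.7
- Denominator: 35 × 13.966 + 140 × 0.846 = 607.3
- Variance 2.744; SE 1.657 s
- Power = Φ(5.275/1.657 − 1.96) = 89.0%, matching the stated 89%

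The yardsticks are therefore an effect of 5.275 s and an SE of 1.657 s.

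**2. How many patients the rule touches.** 0.20 × 330 = 66. The base is uncertain. Six retained per cell gives 6 × 6 × 7 = 252 patients; if those are what is left after 20% loss, 252/0.8 = 315 are enrolled and 63 are lost. The documents do not say how many losses are deaths or inability. Assuming 25% to 75% of the 66 gives 16.5 to 49.5, or roughly 16 to 50 patients.

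**3. TUG, illustration.** Assume the same TUG distribution in both arms among those who can be tested, imputed values averaging 21.1 s, and 60 s as the value that inability should carry. Shift = (share unable, intervention − share unable, control) × (60 − 21.1).

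| Control unable | Intervention unable | Shift missed by imputation |
|---|---|---|
| 2% | 1% | −0.39 s |
| 5% | 2.5% | −0.97 s |
| 10% | 5% | −1.95 s |
| 5% | 10% | +1.95 s |
| 10% | 10% | 0 |

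The largest is 1.945/5.275 = 37% of the planned effect, or 1.945/1.657 = 1.2 SE. Imputation that uses function measures would narrow the gap. If it gave these patients 40 s on average, the 10% against 5% case becomes 0.05 × (60 − 40) = 1.0 s.

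**4. CAS, illustration (deaths only).** Assume the same proportion q of survivors reaches CAS = 6 in both arms. Imputing the dead at q gives a difference of 0. Counting death as not reaching 6 gives q × (control mortality − intervention mortality).

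- q = 0.6, mortality 10% control, 5% intervention: 0.6 × 0.05 = +3.0 points
- q = 0.5 to 0.7, same mortality: +2.5 to +3.5 points
- q = 0.6, mortality 5% control, 8% intervention: 0.6 × (−0.03) = −1.8 points

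**5. Does restricting TUG to survivors cure it?** Suppose the intervention keeps alive an extra 4% of patients who walk in 40 s where others take 16 s, and their control counterparts die. The intervention mean rises by 0.04 × (40 − 16) = 0.96 s. That shift appears if the control deaths are imputed at 16 s, and it appears equally if they are left out.

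Every share, time and mortality rate in steps 3 to 5 is an assumption; none comes from the documents.

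**The case against.** The strongest reply is that this is one sentence in a journal article. It does not say that death counts as missing, mortality is a separate outcome, and an analysis plan not shown could narrow the rule. That is true, and a reader should not infer that the sponsor has decided to impute for the dead. But the article does state a rule, pairs it with intention to treat, and leaves no visible exception. The point concerns what that rule does if followed.

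Three stronger readings are tempting and are not supported:

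- **That immobile patients would receive imputed CAS values.** CAS scores bed transfer, sit-to-stand and gait, so a living patient who cannot walk has an observed low score. For CAS, only deaths matter.
- **That imputed patients would get average values.** Table 3 collects TUG, CAS, Barthel-20, New Mobility Score, grip strength, chair stand, composite physical function and co-morbidity in hospital, and repeats several of these at 8 weeks. A model using them would predict worse function for frailer patients. This reduces the problem for inability but does not create a value for someone who has died. The frailty remark likewise does not prove that data are missing not at random once these measures are used.
- **That the bias is known to run against the intervention.** The direction depends on which arm has more deaths or inability.

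Part of the groundwork also exists. Reasons for dropout are to be examined, non-completers are to be described, and palliative and permanent nursing-home patients are excluded, which plausibly lowers early death and immobility. None of this assigns an outcome to those who die or cannot be tested.

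**Conclusion.** The concern holds in limited form. As written, the rule would produce TUG times for patients who died or cannot perform the test, and 30-day CAS values for patients who died, and no stated sensitivity analysis would reveal the effect. If death or inability differs between arms, either primary contrast can be biased. With equal shares and the same distribution among those who can be assessed, the illustrations give no shift.

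The size and direction cannot be derived from the documents, which give no absolute death rate and no rate of inability. The illustrations run from 0 to about 1.9 s either way for TUG and from −1.8 to +3.5 points for CAS. They show that the effect could matter against a 5.3 s target, not that it will. The change is worth making before analysis.

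**What to change.** Amend the missing-data section, or confirm in the analysis plan, as follows:

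1. Limit multiple imputation to values that exist but were not observed (patient alive and able to be tested, assessment not done). Include arm, step, cluster and the in-hospital and concurrent function measures in the imputation model.
2. Count death before the 30-day assessment as not reaching CAS = 6. Score living patients who cannot walk as observed.
3. For TUG, pre-specify a supporting analysis that gives death and inability a defined worst value: either speed (1/TUG, with 0 for these patients) or worst ranks. Item 1 alone is not enough, because leaving out the dead does not remove the survivor bias (step 5 of the working).
4. Report deaths and inability to perform TUG by arm beside the primary results.
5. Add a delta-adjusted sensitivity analysis in which unobserved values are worse than missing at random predicts.

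The cost is a reason code (dead, unable, other) at the week-8 visit, which extends the existing plan to examine reasons for dropout, and a little more analysis and presentation work. TUG on a speed or rank scale is harder to explain than seconds, which is why it is proposed as a supporting analysis. No extra patients or visits are needed.

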### Plans to give access to the full protocol, participant-level data, and statistical code

Anonymised data will be made accessible on reasonable request and in compliance with national laws.

### Oversight and monitoring

#### Composition of the coordinating centre and trial steering committee

The trial will be organised with a project group responsible for the day-to-day management, data collection, and deliveries of the trial. The project group plan to meet once a month. A steering committee consisting of stakeholders from hospital and municipalities provide oversight and meets quarterly with the project group. To secure the scientific quality, a research group consisting of a senior researcher will be established. The project group and research group plan meetings by demand but intend to meet at least two times a year. An implementation group consisting of physiotherapists and nurses from hospitals and municipalities will also be created. The implementation group will be the project group’s direct contact to the clinicians and offer a forum to overcome challenges and facilitate communication between sectors and municipalities. The implementation group and project group meet once every 2 months.

#### Composition of the data monitoring committee, its role, and reporting structure

A data monitoring committee was not deemed relevant as this is an implementation RCT. The interventions are feasible for the patient group and mainly consist of standardised exercise and enabling exercise by reducing the risk of medical complications and pain.

#### Harms

Given the feasibility of the intervention, no harms are expected.

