#### Intervention description

The intervention will be offered to the intervention group in addition to the usual rehabilitation and care. The intervention is comprehensive and includes rehabilitation, empowerment, and care. The duration of the intervention will be 12 weeks (post-surgery). The basis for the intervention is that continuous and progressive rehabilitation, as well as early detection of critical illness and complication during and after hospitalisation, will improve the older adults’ physical performance. The older adults are expected to be motivated by an empowerment-orientated praxis [14].

Within the first 2 weeks after discharge, rehabilitation in the primary sector comprises five rehabilitation sessions. This will be followed by supervised rehabilitation twice a week for another 10 weeks. The rehabilitation in both sectors will follow a progressive rehabilitation programme including resistance exercise. Progression of resistance follows the national guideline for hip fractures which suggests resistance is added at 3 sets of 15 unweighted repetitions and progresses to 3 sets of 8 repetitions maximum [7]. For patients with a CAS ≥ 4, rehabilitation in a municipal rehabilitation centre will be recommended; alternatively, the resistance exercises will be performed at home with wrist weights. Except for the sit-to-stand exercise, the older adults will be requested to perform the exercises as often as possible, preferably three times a week. The exercise sit-to-stand as many times as possible will be recommended after each of the three main meals a day [15].

In the municipalities, nurses will visit the older adults on the third day after discharge to measure vital signs. Vital signs consist of early detection of illness or complications and pain management, e.g. blood pressure, pulse, respiratory frequency, saturation, consciousness, temperature, and saturation combined with measurement of C-reactive protein and haemoglobin.

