#### Criteria for discontinuing or modifying allocated interventions

Physiotherapists and nurses will be instructed to adapt the exercise to patience individual tolerance. This is to avoid unnecessary harm in terms of exercise-induced pain. Furthermore, patients and health personnel are taught to act and involve hospital doctors or general practitioners if medication needs to be modified.

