#### Other outcomes

*Physical function* is measured using handgrip strength (HGS) which is a biomarker for ageing [27].

*Activities of daily living* will be measured using composite physical function (CPF, 0–24). CPF assesses the patients’ need for help to basic and instrumental activities of daily living [28].

*Pain* will be assessed using the 4-point Verbal Rating Scale (VRS, no pain, slight pain, moderate pain, and severe pain) [29].

*Readmission* will be measured 30 days after discharge.

*Mortality* will be assessed as an event 30 days after discharge and within the first year.

*Quality of life and pain* will be measured using the EuroQol Five-Dimension Questionnaire [30]. EQ-5D is a standardised questionnaire, used to assess the patients’ health-related quality of life and function [31].

*Empowerment* will be assessed using the patient activation measure (PAM) [32]. PAM includes thirteen questions addressing prevention and lifestyle changes.

*Fatigue* will be assessed using the Brief Fatigue Inventory (BFI) [33].

*Collaboration between health professionals* will be assessed using a questionnaire designed by Joint Action Analytics to measure the relational capacity [34] The questionnaires will be distributed before workshops and 3 months after the workshop.

*Costs information* will be collected for a cost-utility analysis [35]. Data from registries, municipalities, and hospitals are gathered retrospectively while information on carers’ and volunteers’ expenses in assisting the older adult in activities of daily living is gathered prospectively.

Costs information and information on the number of supervised training sessions, activity level, pain, place of rehabilitation, and the number of self-training sessions will be collected every 2 weeks for 12 weeks. The patients will be equipped with a diary as a memory aid.

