## Discussion

The project aims to improve physical function in older patients after hip fracture. It is hypothesised that patients in the intervention group will gain a significantly improved physical function compared to patients following usual care.

In the trial, we want to empower patients to self-exercise and to continue exercising after the intervention has ended. We do not expect cognitively impaired patients will be empowered by the stimuli put forward and excluded patients with severe cognitive impairments.

Besides improved physical function, it is important to accentuate that the study operates across sectors and organisational conditions on which the design is based. A clear advantage of the cluster randomised stepped-wedge design is the implementation of the intervention at the end of the trial municipalities and hospitals. By randomising in clusters and introducing incremental rollout, issues such as impaired organisational commitment should be met [42]. Furthermore, the design has been used in previous trials working in the primary and secondary sectors [42, 43]. At the end of the project, the intervention is implemented offering a manual for how interventions may be implemented in other hospitals and municipalities [44]. A drawback of the design is the risk of unequal exposure to seasonal trends.

The primary time of interest was 8 weeks after discharge, because this is comparable to the average duration of usual rehabilitation in municipalities. Guidelines indicate that 50% of older adults after hip fracture have a need of a 12-week intervention in spite additional effect is unknown [7]. We therefore extended the intervention to 12 weeks to evaluate the additional effect.

The implementation of the intervention might pose some challenges due to the needed organisational changes. Furthermore, procedures to monitor the delivery of the intervention have been set up, in terms of structured telephone interviews every 2 weeks. We expect the content of the trolley in form of exercise diaries, information to apps, and exercise equipment will help empower patients and health professionals.

Data on older patients’ activity levels and function enable the evaluation of possible associations between functional improvement and an increase in the level of activity.

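### The Harms section states an expectation in place of a plan, and the article describes no recording of falls, new injuries or exercise stopped because of symptoms

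*Protocol article*

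**What the plan says.** The Harms section consists of "Given the feasibility of the intervention, no harms are expected". It gives no definition, method of collection, time window or form of reporting. The Interim analyses section takes a related position: "No interim analysis has been planned because the interventions delivered have been proved feasible and safe for the intended population". The article cites no evidence there.

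Elsewhere the article does foresee a harm. Under the criteria for modifying the intervention, staff are told to adapt the exercise to the patient's tolerance, and the reason given is: "This is to avoid unnecessary harm in terms of exercise-induced pain". The Sample size section expects 20% dropout, which it attributes to frailty.

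On exercise at home, the Intervention description says: "The exercise sit-to-stand as many times as possible will be recommended after each of the three main meals a day". The other exercises are requested preferably three times a week.

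On data, Table 3 schedules the pain scale (VRS) in hospital, at 2, 4, 8 and 12 weeks, and at 6 and 12 months. It has event rows for re-operation, readmission and mortality. Under Other outcomes, costs, supervised sessions, activity level, pain, place of rehabilitation and self-training sessions "will be collected every 2 weeks for 12 weeks". Reasons for dropout are to be examined. The adherence section describes telephone interviews with patients every 2 weeks for the first 12 weeks after discharge.

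**The concern.** Feasibility shows that a programme can be delivered. It does not show that delivering it causes no falls or injuries, and those are the obvious events to ask about when people recovering from a hip fracture are given added resistance and sit-to-stand exercise. Because the article has a Harms section and fills it with an expectation, this is a stated position and not a detail left to a fuller document.

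The Discussion says that the intervention is in place in the municipalities and hospital at the end of the project and is offered as a manual for others. Those who adopt it would want to know whether falls or injuries rose. Under the plan as described, a fall at home that leads to no re-operation, readmission, death or dropout has no stated place to be recorded. A fall that does lead to one of these would not be identifiable as a fall.

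**Working it through.** No figure in the plan is in dispute. The check sets the lists of collected data against the harms in question, then looks at exposure, contact and timing.

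**1. Where falls and injuries could appear.**

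| Place in the article | Safety-related items | Falls, new injuries, exercise stopped for symptoms |
|---|---|---|
| Primary, secondary and other outcomes | Pain, 30-day readmission, mortality | Not listed |
| Table 3 | VRS pain; re-operation, readmission, mortality | Not listed |
| Fortnightly items | Pain | Not listed |
| Retention section | Reasons for dropout | Only if the patient drops out |

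**2. How much exercise is unsupervised.** Supervised sessions are 5 in the first two weeks plus 2 × 10 = 25, which reproduces the 25 in Table 2. The other exercises, at three a week, give 3 × 12 = 36 sessions.
- If the 36 include the supervised ones: (36 − 25)/36 = 11/36 = 31% unsupervised.
- If they are additional: 36/(36 + 25) = 36/61 = 59% unsupervised.

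Sit-to-stand after three meals a day comes on top. Partly unsupervised holds on either reading.

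**3. Planned contact by condition.** The intervention has 25 physiotherapy sessions, a virtual meeting and a day-3 nurse visit. For usual care, Table 2 gives 1 to 2 sessions a week for 6 to 8 weeks, so 1 × 6 = 6 to 2 × 8 = 16. Its schedule row gives 1 + 7 × 1 = 8 to 1 + 7 × 2 = 15. Staff therefore have more occasions to hear of an event in the intervention condition.

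**4. Room in the existing calls.** Twelve weeks at one call per 2 weeks is 6 calls per patient.

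**5. Effect of a late start.** Two municipalities split in two and four combined into two give 4 + 2 = 6 clusters. Recruitment of 21 months in 3-month steps gives 7 periods. Assume that one cluster crosses per step (the figure is not shown). Control cluster-periods then number 6 + 5 + 4 + 3 + 2 + 1 + 0 = 21, and intervention cluster-periods also 21. If the questions began, for illustration, with period 4, 3 + 2 + 1 + 0 = 6 of 21 control cluster-periods would be covered, against 3 + 4 + 5 + 6 = 18 of 21 intervention ones.

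**6. What a comparison could show.** The article gives no fall rates, so these are assumptions. With 330/2 = 165 patients per condition, ignoring clustering and period effects, two-sided 5% power is 72% for 10% against 20%, 62% for 15% against 25%, and 56% for 20% against 30%. The result should be read as an estimate with an interval.

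**The case against.** The strongest reply is that harm data are not absent. The one harm that the article names, exercise-induced pain, is measured repeatedly on the VRS and asked about every fortnight. Re-operation, readmission and death are recorded, and reasons for dropout are examined. All of that stands. A reader might infer from the Harms sentence that no safety data are collected, and the article does not support that. The gap is confined to falls, new injuries and symptom-driven stopping of exercise.

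The article is also condensed, and its call scripts and forms are not shown. It can be said that the article states no such recording. It cannot be said that these events are never recorded in practice.

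Unequal contact is partly inference too. Exercise diaries go to all patients, the calls are described for patients generally, and usual care includes instruction in self-training. The difference in planned sessions and the lack of assessor blinding remain.

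Three stronger readings are tempting and fail:
- The Discussion's remark "in spite additional effect is unknown" may look like a contradiction of proven safety. It concerns the added benefit of a 12-week programme, and the next sentence says that the extension is meant to evaluate that benefit.
- The data monitoring section may seem to repeat the safety claim. It says "A data monitoring committee was not deemed relevant as this is an implementation RCT" and relies on feasibility. It does not assert proven safety, so there is no such wording to correct.
- One could count every sit-to-stand bout and conclude that nearly all exercise is out of staff view, or compute an upper limit for zero events. The count treats a short bout after a meal as equal to a session of up to 45 or 60 minutes. The limit needs a number of intervention patients that the article does not state, and an absence of falls is hardly plausible in this population.

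**Conclusion.** The point holds in this limited form. The Harms section infers no harm from feasibility, against the article's own anticipation of exercise-induced harm, and no stated data item captures falls, new injuries or exercise stopped for symptoms. Followed as described, the trial cannot compare these events between conditions, and whatever is noted informally is open to bias from unblinded assessment and more frequent contact under the intervention.

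The size is qualitative: one class of safety information is missing, and the primary analyses, sample size and power are unaffected. The change is worth making because the programme is rolled out at the end of the trial and the means of collection largely exist. The conclusion assumes that the unseen forms do not already contain such questions. If they do, the remedy is to say so in the article.

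**What to change.** Replace the sentence under Harms with a short plan. In the existing fortnightly interviews, ask three fixed questions with the same wording and over the same 12-week window in control and intervention periods: any fall, any new injury, and any exercise stopped because of pain or symptoms. Report the answers by condition in one table with pain, re-operation, readmission and death. Under Interim analyses, state the evidence for "the interventions delivered have been proved feasible and safe for the intended population". These changes concern data collection and reporting only and alter no exercise or clinical rule.

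The cost is a few questions per existing call, a form change and one table, with no added visit. There are three downsides:
- Self-reported falls are imperfect, and reporting is unblinded.
- The calls must be confirmed to run in control periods, since the Discussion presents them as a way to monitor delivery of the intervention.
- Recruitment began on 1 October 2020. Questions added later would miss mainly control-period data, so the comparison must be restricted to, or adjusted for, the periods in which they were asked, and the start date must be reported.
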